## Abstract

**Background:**

Alcohol is a major source of harm in Australia that disproportionately affects low-income communities. Alcohol brief interventions (ABIs) combine an assessment of a person’s alcohol use with advice to reduce health risks. Despite their effectiveness, ABIs are not routinely performed by clinicians. This article presents a protocol for a feasibility trial of pragmatic implementation strategies and a new set of resources to support clinicians to complete ABIs in Australian general practices.

**Aim:**

To explore the facilitators and barriers to increasing the uptake of ABIs in primary care, including acceptability, reach, adoption, fidelity, and sustainability.

**Design & setting:**

A mixed-methods evaluation of the uptake of ABIs in general practice clinics serving low-income communities in Melbourne, Australia. The approach is informed by the Consolidated Framework for Implementation Research (CFIR) and Normalisation Process Theory (NPT).

**Method:**

The implementation strategies and resources will be trialled in five general practices over 12 months. The primary outcome will be change in the proportion of adult patients with a complete alcohol history in their electronic medical records. Baseline data collection includes a practice survey to describe practice routines for ABIs and de-identified patient medical record data on completed alcohol histories (repeated at 3, 6, 9, and 12-months post-intervention). Survey and interview data will also be collected from clinicians, patients, and primary health network staff to assess acceptability and feasibility of the intervention.

**Conclusion:**

The study will explore how the implementation strategies and resources can improve alcohol screening and management among low-income patients in general practice.

## How this fits in

Brief interventions for alcohol delivered in primary care are effective for reducing alcohol-related harm. Currently, ABIs are often not routinely delivered in primary care. A new implementation strategy has been developed with supporting resources to increase the uptake of ABIs in primary care. This implementation trial will explore barriers and facilitators to increasing routine delivery of ABIs in primary care, to inform future policy and practice.

## Introduction

### Background and rationale

Alcohol is a major source of harm. Each year, harmful alcohol use contributes to 3 million deaths and the loss of 132.6 million disability-adjusted life years (DALYs).^1^ Low-income communities are at increased risk of alcohol-related harm.^2^ In Victoria, Australia, the burden of the 1200 deaths per year attributable to alcohol^3^ falls disproportionately on the 13% of Victorians living in poverty.^4^

ABIs involve assessing the amount of alcohol a person is consuming and offering individualised advice to reduce the associated health risks.^5^ ABIs provided by GPs and nurses in community-based primary care can reduce the number of episodes of risky drinking and weekly average alcohol consumption among people with problematic alcohol use.^5^ Alcohol-related harms affect more people with harmful alcohol use than those with alcohol dependency, and large reductions in alcohol-related harms can be achieved by reducing alcohol use in the former population.^6,7^

Strong primary care systems are the foundation of equitable healthcare service delivery.^8^ In the setting of alcohol harm, equity is especially important as people from low socioeconomic groups experience a disproportionate amount of harm from alcohol use.^9^ Few trials on the effectiveness of ABIs have considered the specific needs of low-income groups, potentially contributing to greater health disparities.^10^ The overall aim of the project is to: (a) increase screening for problematic alcohol use; and (b) increase the application of ABIs in general practice. The preferential focus on low-income groups will aim to reduce health inequity by ensuring the approach is most acceptable, feasible, and effective for low-income groups.^11^

### Objectives

Mixed methods will be used to assess the acceptability and feasibility of an implementation strategy to increase the uptake of ABIs for alcohol in Australian general practices serving low-income communities.

## Method

This is a single-arm implementation trial using mixed methods to evaluate the uptake of ABIs in primary care. The approach is informed by: 1) the CFIR to assess factors affecting implementation and effectiveness; and 2) NPT to understand how change is embedded in a practice.

### Study setting

The trial will be conducted in five general practice clinics located in northern metropolitan Melbourne, Australia, in a region corresponding to a primary health network (PHN) catchment (PHNs are federally funded to oversee primary care delivery in local regions).^12^

Participating general practice clinics will be located in a low-income area as identified by the PHN; that is, a Socio-Economic Indexes for Areas (SEIFA) score <1000, where a score of 1000 is the mean for all areas, and scores lower than this indicate relative disadvantage. Practices will use electronic patient medical record and billing software compatible with the PHN’s practice data extraction tool (Pen CS CAT4).^13^ Consent will be gained from practice management and at least one GP. No specific eligibility criteria will apply to participating GPs. No clinician in the practice will be mandated to use the resources. Patient participants will be aged >18 years and able to understand eighth-grade English. Interpreters will be used for patient interviews when necessary.

### Intervention

In preparation for this trial, the authors sought to understand participants’ experiences of talking about alcohol in general practice settings and suggestions on how to promote and improve these conversations ([name], [name], [name], *et al*. *Patient and clinician perspectives of factors that influence the delivery of alcohol brief interventions in Australian primary care: A qualitative descriptive study —* under review). Implementation strategies and an associated resource pack to increase the uptake of ABIs in primary care were then co-designed with patients and clinicians (https://www.monash.edu/medicine/spahc/general-practice/research-projects/reach).

NPT^14^ was used as well as 'priming' to construct the approach to implementation. The authors incorporated 'sense making' for clinicians with training and resources on best practices for ABIs, 'relational work' by identifying and supporting practice champions, 'operational work' using in-consultation resources, 'appraisal work' with regular updates to the clinics on alcohol screening rates, and 'priming' the patients with posters and pamphlets to be more receptive to discussions about alcohol. Before the start of the trial, a state of emergency was declared in Australia owing to the COVID-19 pandemic. The intervention was then adapted for use during telehealth consultations (see Supplementary Table S1).

### Ethical issues

Ethics approval has been granted (see statement below). Routine systems are in place to offer assistance and follow-up any patient who is distressed by health-related research. This includes signposting opportunities for support plus personal follow-up at participant request. Survey and interview participants who express concerns about their alcohol use will be directed to seek help from their primary care provider or local drug and alcohol counselling services.

### Intervention process

Before the trial, practices will identify a champion to promote the intervention to their colleagues. Practice engagement staff from the PHN will support implementation at the practice with quarterly visits to provide ongoing feedback on practice performance and to promote use of the clinical resources. This rollout via the PHN was chosen as a pathway to support sustainability for future scale-up.

### Outcomes

The primary outcome is the change in the proportion of adult patients (aged >15 years) with completed alcohol histories in their electronic medical record. Implementation outcomes, informed by RE-AIM (Reach, Effectiveness, Adoption, Implementation, and Maintenance),^15^ include:

Reach: the change in proportion of patient records with information on alcohol status (drinks alcohol; does not drink alcohol) as a proxy marker for where a brief intervention (BI) is likely to have occurred.Acceptability: to patients, clinicians, practice staff, and PHN staff.Adoption within each practice and within the PHN processes.Fidelity of intervention implementation via project timelines completed by the PHN, research team, and member-checked during provider interviews.Sustainability as perceived by practice staff, clinicians, and PHN staff.

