### Data collection methods

Table 1 shows data collection at the patient, provider, practice, and PHN level.

**Table 1. table1:** Data Source and data collection timepoints

Data source	Practice	Provider	Patient	Primary health network
Tool or survey	*Electronic patient database (PENCS CAT4^TM^*^13^)	Practice survey	NoMAD tool^a^	Interview	Patient survey (all)	Interview	Follow-up SMS survey	Interview	Project timelines
Contact point timeline									
Baseline	X	X							
Post- consultation					SMS link	Telephone			
3 months	X						X	X	X
6 months	X		X				X	X	X
12 months	X		X	X			X		X

SMS = short message service.

a Normalisation Measure Development questionnaire.^17^

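### PHN staff are one of three groups whose view defines sustainability, but their interviews stop at month 6 of 12 and are not described as covering it

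*Protocol article*

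**What the plan says.** The Abstract's aim lists the implementation properties to be explored, "including acceptability, reach, adoption, fidelity, and sustainability". The Outcomes section defines the last of these as "Sustainability as perceived by practice staff, clinicians, and PHN staff". Three respondent groups therefore make up this outcome.

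The Method part of the Abstract sets the length: "The implementation strategies and resources will be trialled in five general practices over 12 months". The Intervention process section says that PHN engagement staff will make "quarterly visits to provide ongoing feedback on practice performance and to promote use of the clinical resources". It adds that delivery through the PHN was chosen because it should help the approach last and spread.

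Table 1 ("Data Source and data collection timepoints") gives the schedule. For the PHN it has two columns, an interview and the project timelines. The interview is marked at 3 and 6 months. The timelines are marked at 3, 6 and 12 months.

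The Qualitative instruments section plans interviews with up to five PHN staff, directed at the CFIR outer setting and the influence of policy on implementation. The clinician interview in the same section lists sustainability among its topics.

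**The concern.** The outcome definition and the schedule do not fit for one of the three groups. PHN staff are asked for the last time halfway through the trial, and the described focus of their interview does not include sustainability. A mid-trial PHN opinion on whether the approach can last is a forecast made before the second half of the PHN's own involvement.

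The gap falls on the group the plan relies on most for this question. PHN staff make the practice visits, and the PHN is the intended vehicle for scale-up. Whether the PHN thinks it can keep the work going is central to the sustainability outcome, and the schedule does not ask for that view at the end of the trial.

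**Working it through.** No arithmetic applies and the plan states no figure to reproduce. The check is a reading of Table 1 by column, set against the outcome definition and the instrument descriptions.

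**Step 1: read the schedule.** Table 1 lists nine data columns, and the 3-, 6- and 12-month rows each split into nine fields, so marks can be matched to columns without guessing.

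| Time point | Columns marked |
|---|---|
| 3 months | Electronic database, follow-up SMS, PHN interview, project timelines |
| 6 months | Electronic database, NoMAD, follow-up SMS, PHN interview, project timelines |
| 12 months | Electronic database, NoMAD, provider interview, follow-up SMS, project timelines |

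There are two PHN interview rounds, and the later one is at month 6 of 12 (6/12 = half of the trial period). The Abstract also mentions a 9-month record extract that Table 1 does not list. That concerns records and does not bear on the PHN interview.

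**Step 2: match each defining group to a source for sustainability.**

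| Group in the outcome | Source described | Latest time | Sustainability named? |
|---|---|---|---|
| Clinicians | Provider interview; NoMAD | 12 months for both | Yes, in the clinician interview topics and in Table 2 for NoMAD |
| Practice staff | NoMAD | 12 months | Yes, in Table 2 |
| PHN staff | PHN interview | 6 months | No |

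**Step 3: look for another source of the PHN view.** NoMAD is completed by GPs, practice nurses and administrative staff (Quantitative instruments), or by practice managers and clinicians (Table 2). Neither description includes PHN staff. The project timelines do reach 12 months, but the Outcomes section assigns them to fidelity. The PHN interview is therefore the only described source.

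**Step 4: look for data after support ends.** The Abstract has record data "repeated at 3, 6, 9, and 12-months post-intervention", and the last row of Table 1 is 12 months. The quarterly PHN visits are given no end date, and no phase without them is described. No data point is described after 12 months or after support is withdrawn.

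**The case against.** The strongest reply is that this is a feasibility trial and the outcome is perceived sustainability, not demonstrated maintenance. Two of the three groups are assessed at the end, by instruments tied explicitly to sustainability. Record data to 12 months, collected monthly for the time series according to Table 2, will show whether an early gain holds within the trial. PHN support is also the proposed route at scale, so measuring while it is in place is relevant to that model. What is left affects up to five interviewees and one implementation outcome.

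Much of this stands, and it limits how far the point can go. A reader might infer that all data collection stops while PHN support is still running, so that the design cannot show whether any change lasts and a gain that later faded would be reported as sustained. The documents do not support that:

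- No end date is given for the visits, and the term post-intervention in the Abstract is not defined as after the start or after the end. The overlap of support and measurement is plausible but not stated.
- For the same reason, the share of visits completed by month 6 cannot be counted. Neither their number nor their dates are given.
- Because the outcome is a perception, the absence of post-support data limits interpretation. It does not contradict the definition.

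The reply does not touch the PHN mismatch. Late coverage of clinicians and practice staff does not supply the PHN's own view, and the article itself fixes both the outcome and the schedule, so the mismatch is not a detail left to a fuller document.

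**Conclusion.** The point holds in a narrow form. Of the three groups that define sustainability, one (PHN staff, up to five interviewees) has its last scheduled interview at month 6 of 12. The described focus of that interview does not name sustainability, and no other described instrument fills the gap. The other two groups are adequately covered at 12 months.

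Separately, the design as described supports statements about perceived sustainability and about persistence of recording within the 12 months. It does not assess persistence without PHN support. This is a limitation to be stated, not an error in the outcome.

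The conclusion rests on the column reading of Table 1, which was extracted by a program but is consistent across the three follow-up rows, and on the instrument descriptions being complete as to who answers what.

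**What to change.** 1. In Table 1, move one of the two PHN interview rounds (3 or 6 months) to 12 months, so that two rounds remain.
2. In the Qualitative instruments section, add sustainability to the topics of the PHN interview, alongside the outer-setting focus. A later date alone would not guarantee that the view is collected.
3. State in the article that conclusions on sustainability concern perception and persistence within the 12 months, and that persistence without PHN support is not assessed.

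If a 12-month PHN round is not possible, the alternative is to remove PHN staff from the definition of the sustainability outcome. That is less attractive, given the role the plan gives the PHN.

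The cost is one fewer early PHN round, so less information on how implementation started from the PHN's side. No interviews are added. Extending the record extract beyond 12 months is not needed to resolve this point. It would create a new endpoint tied to a last visit that the plan does not define, and it would lengthen data sharing for the trial clinics and the approximately 850 comparison clinics.

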### Sample size

Five practices will be recruited to evaluate the process of implementation. At least one GP or practice nurse will be formally recruited at each practice; other clinicians will have access to the resources and can participate in team feedback meetings. For the nested short message service (SMS) survey study, 140 patients will be recruited who self-identify as drinking at risky levels across the five practices per the AUDIT-C questionnaire.^16^ The authors are interested in the response rate over time; that is, both the number of responses at each time point, and the number of questions answered at each time point. Changes will also be able to be detected in drinking patterns (10% change total standard drinks per week compared with baseline, power 0.8, significance 0.05).

### Recruitment

#### Practices

The PHN will recruit practices via newsletters and the PHN website. A member of the research team will then contact practice management to explain the project and seek written informed consent.

#### Practice staff

Researchers will ask practice management to circulate information to their clinicians. Interested clinicians will contact the researchers for more information and to provide written consent.

#### Patients

The practice will send an SMS to all patients who visited the practice in the previous 3 months, inviting them to fill in a short survey on their experiences of discussing alcohol with their clinician. Patients will also indicate if they are happy to be contacted for a follow-up survey and/or interview. Follow-up surveys will be sent to participants who self-identify as drinking at risky levels.

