### Quantitative instruments

*De-identified patient data from Pen CS CAT4.*^13^ The PHN receives data from all practices in the catchment relating to completion of patient alcohol histories. A data-sharing agreement will be entered into with the PHN and participating practices to access this data. The PHN will provide data on the patients with complete alcohol histories as determined by recording of 'drinker', 'non-drinker', 'nothing recorded', and 'patient <15 years of age with nothing recorded' in the patient’s electronic medical record. The baseline measure will include all active patients; that is, those with at least three visits in the past 2 years. At 3 months and 6 months, the change in proportion of patients with an alcohol history will be measured by comparing the proportion of patients with at least one visit to the practice in the preceding 3 months who had a complete alcohol history. These measures will be available for all other clinics (approximately 850) in the same catchment area for comparison.*Practice survey*. This will be administered at baseline to collect information about the practice’s structure, staffing, record management systems, patient load and demographics, and processes for patient intake and assessment relevant to ABIs.*NoMAD* (Normalisation Measure Development) *tool.^17^* The NoMAD tool is a quantitative survey to be completed by participating GPs, practice nurses, and practice administrative staff to assess how well ABIs were embedded into everyday practice.*Patient survey*. This will be via SMS to capture data on whether patients were asked about alcohol use, how they found the experience, their alcohol use (AUDIT-C),^16^ and demographics including low income status.*Patient survey for patients with risky alcohol use*. Patients who self-report risky alcohol use (AUDIT-C) in the patient survey will be invited to participate in quarterly follow-up SMS surveys. Information will be collected on:

The average weekly consumption of alcohol in standard drinks.The frequency of episodes of high-risk drinking.The number of attendances at the general practice.

A subgroup analysis based on self-reported low-income status will be completed.

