#### Quantitative analysis

Quantitative data will be analysed descriptively, with means and standard deviations or medians and ranges reported for continuous variables, and proportions for categorical variables. Correlations will be calculated using Spearman rho (ρ) owing to the anticipated non-normal distribution of scores. Repeated measures data will be analysed using a non-parametric statistics such as the McNemar and Wilcoxon signed-rank test. Multiple regressions will be conducted to assess associations between the intervention measures.

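### The SMS invitation is described by the conversation that the survey is meant to count, so it risks selective reply by patients who were asked about alcohol and an overstated asked share

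*Protocol article*

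**What the plan says.** Under Recruitment, Patients, the sampling frame is everyone who attended recently: "The practice will send an SMS to all patients who visited the practice in the previous 3 months". The same sentence gives the topic of the survey, "inviting them to fill in a short survey on their experiences of discussing alcohol with their clinician". Table 1 likewise labels this survey as being for all patients.

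Under Quantitative instruments, the content is wider than that topic: "This will be via SMS to capture data on whether patients were asked about alcohol use, how they found the experience". It also covers AUDIT-C and demographics. The survey then feeds the next stage: "Patients who self-report risky alcohol use (AUDIT-C) in the patient survey will be invited to participate in quarterly follow-up SMS surveys". Sample size sets that cohort at 140 patients. Willingness to be interviewed is collected through the same survey, and Qualitative instruments plans 20 patient interviews.

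Under Outcomes, the primary outcome does not use the survey: "The primary outcome is the change in the proportion of adult patients (aged >15 years) with completed alcohol histories in their electronic medical record". Reach is also taken from patient records. Under Quantitative analysis, categorical data are summarised as plain proportions.

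**The concern.** A patient whose clinician never mentioned alcohol receives an invitation to a survey about discussing alcohol with the clinician. That patient may reasonably conclude that the survey is meant for someone else. Neither section says that patients who had no such discussion are also wanted. Whether a patient replies can then depend on the answer to the question of whether they were asked.

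Two things are at stake.

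- **The asked share.** Among the listed quantitative instruments, this survey is the only one in which patients report whether alcohol was raised. A plain proportion of respondents would carry any selective reply straight through.
- **Who enters the later samples.** Risky drinkers are found only among those who reply. Those whom the clinic never asked are informative about barriers to uptake, which is the stated aim, and the described invitation is least likely to attract them.

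**Working it through.** **What the documents supply.** They give the frame (all patients seen in 3 months), the described topic (discussing alcohol) and the measured item (whether asked). They give no asked share, no survey response rate and no response rate by asked status. There is therefore no figure of the plan's own to reproduce, and the inputs below are assumptions chosen to show a range.

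**Formula.** Let *p* be the true share of invited patients who were asked. Let *r* be the response rate among asked patients divided by the response rate among never-asked patients. Then

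observed asked share = *p·r* / (*p·r* + 1 − *p*).

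**Worked case, *p* = 0.30.**

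- *r* = 1.5: 0.45 / (0.45 + 0.70) = 39.1%
- *r* = 2: 0.60 / (0.60 + 0.70) = 46.2%
- *r* = 3: 0.90 / (0.90 + 0.70) = 56.2%

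**Range over assumed inputs.**

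| True asked share | *r* = 1 | *r* = 1.5 | *r* = 2 | *r* = 3 |
|---|---|---|---|---|
| 20% | 20% | 27.3% | 33.3% | 42.9% |
| 30% | 30% | 39.1% | 46.2% | 56.2% |
| 50% | 50% | 60.0% | 66.7% | 75.0% |
| 70% | 70% | 77.8% | 82.4% | 87.5% |

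**Direction.** The columns above *r* = 1 assume that asked patients reply more. If never-asked patients replied twice as often (*r* = 0.5), a true 30% would read 0.15 / (0.15 + 0.70) = 17.6%, which is too low. The described topic makes *r* above 1 the more plausible case, but nothing in the documents establishes it.

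**Effect on the later samples.** With *p* = 0.30, never-asked patients are 70% of those invited. Among respondents they would be about 61%, 54% or 44% at *r* = 1.5, 2 or 3 (100% minus the observed shares above). If the same *p* and *r* held among risky drinkers, the pool for the follow-up cohort and the interviews would shift to the same extent.

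**The case against.** The strongest reply is that the message itself is not shown. The Recruitment section gives a one-clause summary in a journal article, and the actual SMS may already say that everyone is welcome. Texting all recent attenders and asking whether alcohol was raised both suggest that never-asked patients are wanted. This stands as a limit on what can be claimed, and it leaves a correction to the article as one possible remedy. It does not remove the mismatch between the described topic and the described content.

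Other parts of the reply also stand.

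- A reader might infer that never-asked patients will opt out and that the asked share will be too high. The documents do not support that certainty, because they give no response rate by asked status and the sign could reverse.
- A reader might treat the survey as the trial's check on the recorded alcohol histories. The article never gives it that role. A patient-reported asked share is not among the listed outcomes, and the patient-survey row of Table 2 concerns only SMS response rates.
- Handling of survey non-response is commonly left to an analysis plan, so its absence here is not a fault.
- The 140-patient cohort is meant to study response over time and change in drinking against baseline, neither of which estimates how often clinicians ask.
- Interviewees are chosen purposively, with variety in how they report the consultation. This softens the effect on the interviews, but the choice can be made only among people who replied to the survey.

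**Conclusion.** The point holds as a risk. As described, the invitation is tied to the event that the survey is meant to count, so reply can depend on the answer. The likely direction is overstatement of the patient-reported asked share, and under assumed inputs the size could be material: a true 30% reading as 39% to 56% for response ratios of 1.5 to 3. Those figures rest entirely on the assumed ratio and on the article's summary being a fair account of the message. There is a related risk that never-asked risky drinkers are under-represented in the follow-up cohort and the interview pool.

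A reader might go further and conclude that the trial's main result is biased. It is not touched, because the primary and reach outcomes come from medical records and not from this survey. The matter is a cheap improvement to a secondary descriptive survey, but it has to be made before the message is sent, since the asked status of non-responders cannot be recovered from the survey afterwards.

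**What to change.** Word the invitation neutrally, for example as a short survey about the recent visit and health topics including alcohol, and add a line such as *please reply whether or not alcohol was discussed*. If the actual SMS already says this, correct the description in the Recruitment section instead.

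Where the data allow, report the survey response rate and compare respondents with all invited patients. Describe the asked share as a share of respondents. Do not present age-sex standardisation as a correction: it would leave selection on having been asked in place within each age and sex group.

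The cost is an edit to the SMS with an ethics notification and a small amount of extra descriptive reporting. No additional patients are needed. The asked share may look less favourable.
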